### Trial design

The *effectiveness-implementation hybrid design* [12] comprises a closed cohort stepped–wedge cluster randomised controlled trial supported with implementation frameworks to test the implementation strategy and the outcomes of the intervention. A stepped–wedge cluster randomised controlled trial design is considered appropriate for implementation evaluations of health service interventions as it simplifies data collection procedures, supports logistical processes better, aligns with ethical principles, accommodates temporal issues, and optimises financial constraints. The stepped–wedge cluster randomised controlled trial addresses the ethical dilemmas of randomised trial design where essential investigations and/or best-practice treatments may be withheld from control participants [12].

The closed cohort stepped–wedge, cluster randomised controlled trial design involves a sequential rollover of the intervention at four local health district clusters after baseline. This study will be conducted in four local health districts in NSW, Australia. Each cluster will begin in the control condition (baseline data collection) and will sequentially receive the intervention at 6-week intervals.

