### Setting

This study will include all patients presenting to one of 30 emergency sites across four local health districts in NSW, Australia (24 EDs/6 multi-purpose services). Multipurpose services provide flexible services to regional and remote communities with integrated health and aged care services [18]. The sites vary in size and are in rural, regional, and urban contexts. The number of sites varies with the geography of each cluster, representing real-world conditions. The sites combined employ approximately 1300 emergency nurses and see over 650, 000 presentations per year (Table 1).

**Table 1 Tab1:** Local health district (LHD) clusters: ED patient and nurse numbers; patient treatment times; and experience

Cluster	ED patients per year (2020–2021)	Patients (%) whose treatment started within recommended timeframes by triage category			ED nurses	Patient rating (%) ‘very good’ care (2019–2020)
		Cat 2 (10 min), target 80%	Cat 3 (30 min), target 70%	Cat 4 (60 min), target 70%		
Northern NSW (8 EDs, 3 MPS)	198,380	69	70	76	430	70
Sydney LHD (3 EDs)	163,839	48	67	81	402	65
Western Sydney LHD (4 EDs)	197,279	28	52	69	280	48
Southern NSW (8 EDs, 4 MPS)	107,073	66	71	79	180	69
Total (30 EDs/MPS)	666,571	53	65	76	1292	63

*MPS* Multipurpose service, *ED* Emergency department

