### Sample size

Sample size calculations considered the estimated between-cluster variance, i.e. between local health district variance, and the design effect associated with the stepped-wedge design [33]. Calculations were based on previous studies and local health district information. Not many previous similar cluster randomised studies have reported the intraclass correlation coefficient (ICC). One similar study on ED LOS used an ICC of 0.18 [34] and another one in community outpatient services but examined waiting time after triage used an ICC of 0.01 [35]. To be conservative, an ICC of 0.05 has been applied in the calculation. Sample sizes relative to the hypotheses are below:
*H1: Patient LOS in ED is 1 h shorter*: The number of ED presentations required per data collection time point at each cluster is 1420 to detect a 1-h change in ED LOS for a two-sided test (80% power; α < 5%), assuming a standard deviation of 5.4 h [36].H2: There is a 5% increase in care started in the national timeframe: To detect at least a 20% increase for Triage Cat 2 and 3 patients, a total of 1920 patients will be required (120 per local health district per quarter).H3: There is a 20% faster time to analgesia: To detect at least a 5% reduction in time to analgesia, 960 patients will be required (60 per local health district per quarter). This is achievable for our 20% target.H4: 5% more patients report ED experience as ‘very good’: To detect at least a 5% increase in the rating as ‘very good’ in the intervention group, compared with the control group, 1920 patients will be required (120 per local health district per quarter).

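### H3: 960 patients detect a 5% reduction in time to analgesia only if its SD is about 0.16-0.17 of the mean (0.28 without clustering); the 20% target depends on a spread that is not printed

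*Protocol article*

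**What the plan says.** The hypothesis is "H3: There is a 20% faster time to analgesia". The sample-size statement under it uses a different effect: "To detect at least a 5% reduction in time to analgesia, 960 patients will be required (60 per local health district per quarter"). It adds: "This is achievable for our 20% target".

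The opening of the same section says that the calculations allowed for between-district variance and "the design effect associated with the stepped-wedge design", and "To be conservative, an ICC of 0.05 has been applied in the calculation". Error rate and power appear only under H1: "for a two-sided test (80% power; α < 5"%). The only SD printed in the section is 5.4 h, for ED length of stay (H1). No mean, SD or log-SD is printed for time to analgesia.

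Trial design describes a "sequential rollover of the intervention at four local health district clusters after baseline". Statistical methods specifies mixed models with fixed terms for intervention status and for time point.

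**The concern.** A relative reduction of 5% in a waiting time is a small effect, and 960 patients in four clusters is a small sample for it. The article need not print every input, so the missing SD is not the complaint. The complaint is that the printed pair, 960 patients and a 5% reduction, implies a spread far narrower than ED times are likely to have. The sentence on the 20% target then borrows its reassurance from that pair.

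If H3 were audited on about 960 records in the belief that even 5% is within reach, a null result could be read as evidence against faster analgesia when the sample could not have shown it.

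**Working it through.** **The plan's own figure.** 60 patients x 4 districts x 4 quarters = 960, so the split reproduces. The 960 itself cannot be derived without a spread, so I solved for the largest spread at which it holds.

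**Inputs.** N = 960, reductions of 5% and 20%, ICC 0.05 (all Sample size, H3 and opening text); two-sided 5% and 80% power (printed for H1, assumed for H3), so z = 1.960 + 0.842 = 2.802; four districts, fixed periods, random district effect (Trial design, Statistical methods). CV means SD/mean.

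**Step 1: no clustering, 480 v 480.** The SE of the relative difference is CV x sqrt(2/480). Setting 0.05/SE = 2.802 gives CV = 0.05 x sqrt(240)/2.802 = **0.276**. Total N = 4 x (2.802 x CV/0.05)^2, which is about 3,140 at CV 0.5 and 12,560 at CV 1.0. Power with 960 is 34% and 12% respectively.

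**Step 2: stepped wedge, ICC 0.05.** Four quarters and a baseline plus four steps imply different numbers of periods, so I used two layouts that both total 960: 4 periods x 60 per district and 5 periods x 48 per district. The generalised least squares SE of the treatment term, per unit of total SD, is 0.1086 (4 x 60) and 0.1122 (5 x 48).

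- Raw scale, 5%: CV limit = 0.05/(2.802 x SE) = 0.164 and **0.159**.
- Log scale, 5%: log-SD limit = -ln(0.95)/(2.802 x SE) = 0.169 and 0.163. At values this small, log-SD and CV nearly coincide.

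Hand check of 5 x 48 with the stepped-wedge design effect (k = 4 steps, one baseline measurement, one measurement per step, n = 48):

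- [1 + 0.05(192 + 48 - 1)]/[1 + 0.05(96 + 48 - 1)] x 3(0.95)/[2(4 - 0.25)] = (12.95/8.15) x 0.38 = 0.604.
- The 192 patients per period are then worth 192/0.604 = 318 independent patients, and 0.05 x sqrt(318/4)/2.802 = 0.159.

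Sensitivity for 5%: over ICCs of 0.01 to 0.18, both layouts and both scales, the limit stays within 0.159-0.181. Five periods of 60 (N = 1,200, more than the plan states) give 0.177-0.182 at ICC 0.05.

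**Step 3: is that spread credible?** With the one SD the section prints, 5.4 h for length of stay, a CV of 0.17 would need a mean stay of 5.4/0.17 = 31.8 h, and 0.28 would need 5.4/0.28 = 19.3 h. This is a benchmark from another ED time, not a measurement of time to analgesia.

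**Step 4: what 960 delivers at wider spreads (ICC 0.05, range over the two layouts).** For a lognormal time, log-SD = sqrt(ln(1 + CV^2)). Each pair shows raw scale / log scale.

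| CV | log-SD | Power for 5% | Power for 20% | Reduction detectable at 80% power |
|---|---|---|---|---|
| 0.5 | 0.47 | 14-15% / 16-17% | 95-96% / 99% | 15-16% / 13-14% |
| 0.75 | 0.67 | 9% / 10-11% | 66-69% / 85-87% | 23-24% / 18-19% |
| 1.0 | 0.83 | 7% / 8% | 43-45% / 67-69% | 30-31% / 22-23% |

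**Step 5: limits for 20%.** Raw scale: 0.20/(2.802 x SE) gives a CV of 0.64-0.66. Log scale: -ln(0.80)/(2.802 x SE) gives a log-SD of 0.71-0.73, which is a CV of 0.81-0.84 if the time is lognormal. Without clustering the raw-scale limit is 1.11.

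**The case against.** **The inputs are unseen.** The section says that it drew on earlier studies and district information, and a condensed article may leave out an SD. This stands as a limit: the conclusion is conditional on the spread. It does not rescue the 5% claim, because the spread required is so narrow.

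**It may be a transposition.** H2 is titled 5% and sized for 20%, while H3 is titled 20% and sized for 5%. If 960 was computed for 20%, it is a plausible number. The printed 5% claim is then still wrong, and the sentence on the 20% target would describe the planned effect with no margin in hand.

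**Table 1 does not settle the spread.** A reader might take its total row, "Total (30 EDs/MPS) 666,571 53 65 76 1292 63", as proof of wide dispersion. It reports treatment start, not analgesia, by triage category, and gives no SD. Its 53 is also the simple mean of four district percentages, (69 + 48 + 28 + 66)/4 = 52.75. It is background at most.

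**The sample may be much larger.** 960 is a requirement and not a stated cap. Participants includes all presentations in the collection period, and Statistical methods uses all data collected. This stands and limits the harm: a misleading null arises only if H3 is confined to about 960 records, which the protocol does not say.

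**Conclusion.** The claim that 960 patients detect a 5% reduction does not hold at any spread that is plausible for this outcome. It needs a CV of at most about 0.16-0.17 under the stated design, or 0.28 if clustering is ignored altogether. At CVs of 0.5 to 1.0 the stepped-wedge power for 5% is about 7-17%.

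A reader might go further and infer that the 20% target is out of reach. The documents do not support that. Whether 960 is enough for 20% turns on a spread that is not printed and on an analysis scale that is not fixed. At a CV of 0.75, for example, 960 is enough on the log scale (85-87% power) and short on the raw scale (66-69%). The 20% sentence is unsupported as written, not shown to be false.

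The figures assume that H1's error rate and power apply to H3, an ICC of 0.05 at district level and equal numbers per cell. They use normal theory with four clusters, and leave out ED-level and repeat-patient correlation and any small-sample correction. This is a stated design claim that should be corrected. It does not threaten the conduct of the trial.

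**What to change.** In the H3 sample-size text:

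1. State which effect, 5% or 20%, 960 was computed for, with the SD or log-SD, the analysis scale, the power and the design effect.
2. Replace the 5% claim with the reduction that 960 patients detect at 80% power under the stated model. On the log scale with a lognormal time this is about 13-14% at CV 0.5, 18-19% at 0.75 and 22-23% at 1.0. Say whether the spread quoted is a CV or a log-SD, because the two diverge at these values.
3. Keep the sentence on the 20% target only if the baseline spread supports it (Step 5 limits).
4. State that 960 is a minimum and that H3 uses all eligible records with an analgesia time.
5. Reconcile the four quarters in the sample-size text with the baseline plus 6-week steps in Trial design, so that the number per district per period is clear.

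The cost is a few reworded sentences and one calculation from baseline data. The stated detectable effect becomes less favourable. No extra patients are needed.

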### Participants

There will be four participant groups in this trial:
*ED patients (medical record audits)*: Routinely collected patient-level medical record data including patient presentation information and costing data will be analysed. All patients (adult and paediatric) presenting to the ED during the collection period for each cluster will be included. Patients requiring immediate resuscitation or direct transfers/admissions from other sites will be excluded from the data.
*ED nursing staff (surveys)*: All registered nurses permanently employed in the EDs/multi-purpose site across each local health district will be invited to participate in pre- and post-implementation surveys.
*ED medical staff (surveys)*: All medical staff employed regularly in the EDs/multi-purpose site across each local health district will be invited to participate in pre- and post-implementation surveys.
*ED patients /carers (surveys)*: Any patient with an ED visit during the survey data collection time will be included. A carer may also complete the survey for paediatric patients under 18 years or patients with cognitive disabilities. Patients with a triage category of one (immediate) or presenting for end-of-life care will be excluded, as well as patients or their carers with cognitive impairment, such as intoxication or dementia.

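### H4's 1,920 patients give about 25–27% power, not 80%, for a 5-point rise in 'very good' ratings; separately, H2's 1,920 is calculated for a 20% rise although its hypothesis is 5%

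*Protocol article*

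**What the plan says.** The Sample size section states the H4 target as "To detect at least a 5% increase in the rating as ‘very good’ in the intervention group", and continues that, "compared with the control group, 1920 patients will be required (120 per local health district per quarter"). No baseline rate, power or significance level is printed for H4. Power and alpha appear only under H1 (80%, two-sided 5%). An ICC of 0.05 and a stepped-wedge design effect are said to apply. The only experience baseline is in Table 1 (Setting), in the column "Patient rating (%) ‘very good’ care (2019–2020", where the overall figure is 63%.

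For timeliness of care the hypothesis reads "H2: There is a 5% increase in care started in the national timeframe", but the calculation under it reads "To detect at least a 20% increase for Triage Cat 2 and 3 patients, a total of 1920 patients will be required", again 120 per district per quarter.

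Three design statements bear on the formula. The trial "comprises a closed cohort stepped–wedge cluster randomised controlled trial" (Trial design), with a baseline and then one of four districts crossing over every 6 weeks. For the record data, "All patients (adult and paediatric) presenting to the ED during the collection period for each cluster will be included" (Participants), and the experience survey takes any eligible patient with a visit in the survey window. The Statistical methods section plans mixed models with fixed terms for intervention status and measurement time point.

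**The concern.** A four-cluster stepped wedge that samples different patients in each period, and estimates period effects, cannot detect a given difference with fewer patients in total than a simple individually randomised comparison needs when nothing is lost to clustering or time. The H4 figure is below that floor. The section also attaches the same 1,920 to a 5% increase (H4) and a 20% increase (H2), both in proportions of similar size.

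H4 is one of five named hypotheses and rests on survey responses, so its sample size matters in practice. If the survey stops near 1,920, a true 5-point gain would be missed about three times in four. Readers who rely on the printed figure could then take a non-significant result as evidence against a gain of that size.

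**Working it through.** **Inputs.** From the documents: 4 districts; baseline plus 4 steps; ICC 0.05 (0.01 and 0.18 are the two values cited from other studies); 120 per district per quarter; Table 1 rates of 63% 'very good', 53% Category 2 and 65% Category 3. Assumed for H2 and H4: 80% power and two-sided 5%, as printed for H1; 5% read as 5 points unless stated.

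**1. The stated total.** 120 × 4 districts × 4 quarters = 1,920.

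**2. Reproducing it.** Per group, n = (1.960 + 0.842)² × [p₁(1−p₁) + p₂(1−p₂)] / (p₂−p₁)². The standard stepped-wedge design effect, with one measurement at baseline and one after each of k = 4 steps, is

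DE = [1 + ρ(kn + n − 1)] / [1 + ρ(kn/2 + n − 1)] × 3(1−ρ) / [2(k − 1/k)].

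With ρ = 0.05 and n = 120: DE = 30.95/18.95 × 0.38 = 0.6206.

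- 53% to 58%: 1,547 per group, 3,094 in total; × 0.6206 = 1,920.
- 63% to 68%: 1,415 per group, 2,830 in total; × 0.6206 = 1,756.

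So 1,920 is matched from the Category 2 timeliness rate, not from the experience rate. When each period has different patients, this product is the number needed per period. Taken that way (480 per district per period, 9,600 over five periods), power is about 81–83% for 63% to 68% and 77–79% for 53% to 58%, as it should be if 1,920 was derived per period.

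**3. Most favourable case for H4: individual randomisation, no clustering.** With 960 per group, SE = √(0.4507/960) = 0.0217. Power = Φ(0.05/0.0217 − 1.960) = 64%. For 80% power, 2,830 are needed.

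**4. H4 under the planned model.** Generalised least squares on district-by-period means, with fixed period effects and a random district effect (Hussey–Hughes). Each mean has variance σ²(1−ρ)/n + ρσ², and the covariance within a district is ρσ², with σ² = 0.655 × 0.345 = 0.226. Power = Φ(0.05/SE − 1.960); detectable difference = 2.802 × SE. The bracketed value treats 0.226 as the within-district rather than the total variance.

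| Layout of 1,920, ICC 0.05 | SE | Power, 63% to 68% | Detectable at 80% |
|---|---|---|---|
| 120 × 4 districts × 4 periods | 0.0371 (0.0381) | 27% (26%) | 10.4 (10.7) points |
| 96 × 4 districts × 5 periods | 0.0381 (0.0391) | 26% (25%) | 10.7 (11.0) points |

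The four-period layout is the five-period design without its last period. Dropping the baseline instead gives the same power. Across ICC 0.01 to 0.18, power stays at about 25–30%. A relative 5% (63% to 66.15%) gives 12–13%. For 80% power at 5 points, the same model (ICC 0.05, five periods) needs about 447 per district per period: 447 × 4 × 5 = 8,940.

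**5. H2 at 1,920, same model, ICC 0.05.**

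| Effect | From 53% (Cat 2) | From 65% (Cat 3) |
|---|---|---|
| +5 points (the hypothesis) | 23–25% | 25–28% |
| +20% relative (the calculation) | 74–79% (to 63.6%) | 94–96% (to 78%) |

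**The case against.** The strongest reply is that the article prints no formula, baseline, power or alpha for H4, and that 1,920 is a minimum. The survey is open to any eligible patient in its window, so more may respond. H4 is also only one of five hypotheses, and H1 has its own calculation. Part of this stands: nothing shows that the survey will stop at 1,920, so low power in the completed trial is a risk and not a certainty. It does not rescue the printed figure. The text says this number is what a 5% increase requires, and no ICC from 0.01 to 0.18, and neither reading of 5%, makes it adequate.

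Four stronger readings are tempting, and the documents do not support them.

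- **That H2 also claims 1,920 for a 5% increase.** It states 1,920 for 20%, and at 20% relative that size is roughly adequate. The H2 fault is the mismatch with its hypothesis. Its outcome comes from routine records at sites with 666,571 presentations a year, so the number analysed should far exceed 1,920.
- **That the cause is established.** Using a per-period product as a total fits well, and a closed cohort of patients would invite that slip. But the match needs 53%, a timeliness rate, while the experience rate of 63% gives 1,756. It remains an inference.
- **That power is as high as 31%.** That value belongs to 120 per district over five periods, which is 2,400 patients.
- **That 'closed cohort' proves a patient cohort was assumed.** The label may refer to the fixed set of EDs.

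**Conclusion.** The point holds for H4. A total of 1,920 does not give 80% power for a 5-point rise from 63%. It gives about 25–27% under the planned model at ICC 0.05, and 64% even if clustering and time are ignored. The detectable difference is about 10–11 points, twice the hypothesised gain. This rests on the Table 1 baseline, on the power and alpha printed for H1, and on a district effect that is constant over time. The conclusion does not depend on how the error arose.

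For H2 the finding is an internal inconsistency between a 5% hypothesis and a 20% calculation. The low power (about 23–28%) applies only if 5 points is the target and only 1,920 records are used.

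**What to change.** 1. **H4:** state that 1,920 gives about 25–27% power for +5 points, or that it detects about +10–11 points with 80% power (ICC 0.05, baseline 63%). Print the baseline, power and alpha, and say whether 5% is absolute or relative.
2. **H2:** reconcile the 5% hypothesis with the 20% calculation, and base the stated precision on the routinely collected presentations that will be analysed.
3. **Formula:** reconcile the closed-cohort label in Trial design with the new presentations in each period described under Participants. Reconcile the quarters in Sample size with the 6-week steps in Trial design. Then use the formula for that design and say whether each number is per period or in total.

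The cost is wording in two sections. No extra patients are needed. The drawback is that the stated H4 figure becomes less favourable.

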### Statistical methods

For each outcome of interest, data collected across all measurement periods and all study data collection time points will be used to compare intervention status (pre versus post). Analyses will apply the intention-to-treat principle. Patient data will be analysed according to the status of the study EDs (i.e. pre- or post-intervention) where patients were presented and treated. Outcomes will be assessed at the patient level using mixed effect models, considering the correlation of patient presentation within ED and local health district (cluster) and multiple presentations for the same patient, with adjustment for potential confounding factors. For example, for ED LOS analysis, we will adjust for patient characteristics, e.g. age and gender and clinical characteristic, e.g. number of laboratory tests ordered. The mixed models will also incorporate fixed terms for intervention status and measurement time points (including baseline). The analyses will include multiple time points pre- and post-intervention. The study design will allow us to determine temporal changes in system effectiveness, e.g. if ED LOS continues to decrease over time.

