### Randomisation

Each cluster will be randomised independently by the research team to 1 of 4 dates until all EDs have been exposed. The clusters will be randomised using a computer random number generator to the dates that will implement. Once the initial randomisation of clusters has occurred, all investigators will know the order in which implementation will occur. However, study clusters will be blinded for the analysis.

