### Cost-effectiveness

The cost-effectiveness analyses will comprise bivariate multi-level models (accounting for relevant confounders including potential secular trends (fixed effects), within site clustering (random effect)) with alpha < 0.05 and correlation between costs and outcomes. Costs related to the EPIC-START (staffing time, education programme) and ED presentations will be incorporated into the analysis using a combination of financial trial records, wage rates, and linked ED data. The incremental cost-effectiveness ratio (ICER) will be calculated from the perspective of the health service to estimate the cost per ‘hour of patient length of stay’ prevented with a time horizon of the hospitalisation period. Discrete event simulation (stochastic) modelling will also be undertaken following best practice recommendations to estimate local health service and Australian system-wide implications (costs and effects) of the sustained implementation of EPIC-START over 5- and 10-year time horizons (discounting at 5%, consistent with Australian recommendations) using trial data and Australian health service profiles to inform assumptions (and probabilistic sensitivity analyses). Economic analyses will be conducted.

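### The LOS model names no LHD-by-period component and no few-cluster inference, with four randomised LHDs that each cross over alone; if that is the whole model, its nominal 5% test is too liberal whenever LHDs drift apart over time

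*Protocol article*

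**What the plan says.** Under Trial design, the protocol article says that the study "involves a sequential rollover of the intervention at four local health district clusters after baseline" and that clusters "will sequentially receive the intervention at 6-week intervals". Under Randomisation, "Each cluster will be randomised independently by the research team to 1 of 4 dates until all EDs have been exposed". With four clusters and four dates, each LHD crosses over alone.

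Statistical methods sets out patient-level analyses "using mixed effect models, considering the correlation of patient presentation within ED and local health district (cluster) and multiple presentations for the same patient". It adds "fixed terms for intervention status and measurement time points (including baseline"). Sample size gives one ICC, 0.05, and no correlation between periods. The cost model, under Cost-effectiveness, names "within site clustering (random effect") as its random effect.

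None of these sections names an LHD-by-period or ED-by-period effect, a denominator-df method or a randomisation-based test. None says that the LHD or ED effects are constant over time, and none rules out period-varying terms.

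**The concern.** A common time effect removes what happens to all LHDs together, and an LHD effect removes what is always different about one LHD. Neither removes a change specific to one LHD in one period. Because one LHD switches at each step, such a change enters the intervention estimate, in either direction depending on when it falls. A model without a term for it judges the estimate by patient-level noise alone.

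The Participants section takes in all presentations apart from resuscitations and direct transfers or admissions, so the patient-level noise is tiny and the reported standard error keeps shrinking. The information about LHD drift does not grow: it comes from four LHDs and a handful of periods. At stake are the confidence interval and p-value for H1, and for any other outcome analysed on all presentations.

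**Working it through.** **Inputs from the protocol article.** Four LHDs with 11, 3, 4 and 12 sites (Table 1); six-week steps; SD 5.4 h, ICC 0.05, a 1 h effect and 1,420 presentations per LHD per time point (Sample size, H1, "for a two-sided test (80% power; α < 5"%)). Table 1 volume: 666,571 / 4 × 6/52 = 19,228 per LHD per six weeks on average (12,355 to 22,890 by LHD), before exclusions.

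**Assumptions.** Five periods (baseline plus four steps). Cluster autocorrelation (CAC), the share of LHD variance that is constant over time, is not given in the document; I use 0.80 to 0.99.

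**The plan's own figure.** A simple two-group comparison needs 458 per arm. A stepped-wedge model with time-constant LHD effects needs 143 per LHD-period, so 1,420 is not reproduced. A CAC of about 0.88 would give 1,392. That mismatch is a separate matter and does not decide this one.

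**Information in the layout.** Code the 4 × 5 staircase as 0/1 and remove LHD and period means: 10 − 6 − 7.5 + 5 = 1.5.

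**Standard errors.** Total variance is 5.4² = 29.16.
- Model SE = √[29.16 × 0.95 / n / 1.5]. At n = 1,420 this is 0.114 h; at n = 19,228 it is 0.031 h.
- True SE = √[(29.16 × 0.95 / n + 29.16 × 0.05 × (1 − CAC)) / 1.5]. At CAC 0.90 it is √[(0.0195 + 0.1458) / 1.5] = 0.332 h at n = 1,420, and 0.313 h at n = 19,228.
- Ratio R = √[1 + n × 0.05 × (1 − CAC) / 0.95]. Size of the nominal 5% test = 2 × [1 − Φ(1.96 / R)].

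| CAC (assumed) | LHD-period SD, h | R, n = 1,420 | Type I error | R, n = 19,228 | Type I error |
|---|---|---|---|---|---|
| 1 | 0 | 1.0 | 5% | 1.0 | 5% |
| 0.99 | 0.12 | 1.3 | 14% | 3.3 | 56% |
| 0.95 | 0.27 | 2.2 | 37% | 7.2 | 79% |
| 0.90 | 0.38 | 2.9 | 50% | 10.1 | 85% |
| 0.80 | 0.54 | 4.0 | 62% | 14.3 | 89% |

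A simulation with 30 EDs in the actual layout gave 14.4% and 90.0% at the two extremes.

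**Where the result is smaller or larger.**
- Drift only at ED level averages out within an LHD. Type I error is 7–32% at n = 1,420 and 27–76% with all presentations. Rough check with equal-sized sites: multiply the drift term by the mean of 1/11, 1/3, 1/4 and 1/12, which is 0.19; this gives 7–32% and 25–75%.
- The sizes stated for H2–H4 are 60 or 120 per LHD per quarter. Read as LHD-period sizes at ICC 0.05, they give 5–12% and 6–19%.
- The two other ICCs cited under Sample size: 0.01 gives 7–32% at n = 1,420; 0.18 gives 33–81%, and 77–95% with all presentations.

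**Few clusters.** With an LHD-period term fitted, the cell-level residual df are 20 − 4 − 4 − 1 = 11. A z-test then has a size of 7–8%; t on 11 df gave 4.7–5.4% in simulation.

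**H1 power with that term and t on 11 df, n = 1,420.** It is 96%, 79% and 53% at CAC 0.95, 0.90 and 0.80, against nearly 100% under time-constant effects. Fixed rather than random LHD effects lower the last two by about one percentage point.

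**The case against.** The strongest reply is that the model is being read from silence. This is a condensed article, its analysis plan is not shown, and random-effect structure, df methods and permutation checks are ordinary content of such a plan. That stands in part: a reader might infer that the article states time-constant effects and large-sample z-tests, and it states neither. It does, however, list the correlations and the fixed terms, and following that list as written with all presentations produces the problem. The point is therefore conditional, but it is not empty.

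A reader might also take 14–89% as a property of the plan, or say that standard errors are several times too small throughout. The documents support neither. The range needs an assumed autocorrelation, ICC 0.05 and drift at LHD level, and at its 14% end the ratio is only 1.3.

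Extending the large figures to H2–H4 is not supported at their stated sizes. Nor is the cost model shown to fail because it names sites and not LHDs: sites are nested in LHDs, so site effects largely absorb constant LHD differences. What it lacks is the period-varying term, and no cost calculation was made.

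The section on methodological considerations and risks lists record-system changes, COVID-19, natural disasters and competing projects as foreseeable, with mitigation in place. It does not call them LHD-specific, and shared events are absorbed by the time effects. They make drift plausible; they do not establish its size.

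**Conclusion.** The concern holds in conditional form. The article names correlation within ED, LHD and patient plus common time effects, and neither a period-varying component nor few-cluster inference, for a trial with four randomised units. If that is the complete model, the LOS test keeps its 5% level only when there is essentially no LHD- or ED-specific drift. Otherwise the size for LHD-level drift is about 14–62% at 1,420 per LHD-period and 56–89% with all presentations, over an assumed autocorrelation of 0.99–0.80 at ICC 0.05 and five periods. Even the mildest of these, an LHD-period SD of 0.12 h or about 7 minutes, matters once all presentations are used. The case is strongest for H1 and for other outcomes analysed on all presentations.

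**What to change.** - Add LHD-by-period and ED-by-period random effects to the LOS model and to every other outcome analysed on all presentations. Add the same period-varying term to the cost model.
- Test the intervention with a small-sample correction: Kenward-Roger, or t on the cell-level residual df. These are 11 with five periods and 16 − 4 − 3 − 1 = 8 with four, so the number of periods should be stated. The H2 total of 1,920 at 120 per LHD per quarter implies four quarters.
- Optionally, report a permutation test over the 4! = 24 orders as a sensitivity analysis. Its smallest attainable p-value is 1/24 = 0.042.
- State the assumed autocorrelation and restate H1 power on that basis.

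If the analysis plan already contains these terms, one sentence naming them settles the point. Otherwise the change is to wording and code, best made before outcome data are analysed. The price is wider intervals: at autocorrelation 0.90 and n = 1,420, the H1 standard error is about 0.33 h instead of 0.11 h.
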